## Abstract

**Background:**

Children with congenital heart disease (CHD) are at increased risk for behavioral, emotional, and cognitive problems. They often have reduced exercise capacity and participate less in sports, which is associated with a lower quality of life. Starting school may present more challenges for children with CHD and their families than for families with healthy children. Moreover, parents of children with CHD are at risk for psychosocial problems. Therefore, a family-centered psychosocial intervention for children with CHD when starting school is needed. Until now, the ‘Congenital Heart Disease Intervention Program (CHIP) – School’ is the only evidence-based intervention in this field. However, CHIP-School targeted parents only and resulted in non-significant, though positive, effects as to child psychosocial wellbeing. Hence, we expanded CHIP by adding a specific child module and including siblings, creating the CHIP-Family intervention. The CHIP-Family study aims to (1) test the effects of CHIP-Family on parental mental health and psychosocial wellbeing of CHD-children and to (2) identify baseline psychosocial and medical predictors for the effectiveness of CHIP-Family.

**Methods:**

We will conduct a single-blinded randomized controlled trial comparing the effects of CHIP-Family with care as usual (no psychosocial intervention). Children with CHD (4–7 years old) who are starting or attending kindergarten or primary school (first or second year) at the time of first assessment and their families are eligible. CHIP-Family consists of a separate one-day workshop for parents and children. The child workshop consists of psychological exercises based on the evidence-based cognitive behavioral therapy Fun FRIENDS protocol and sports exercises. The parent workshop focuses on problem prevention therapy, psychoeducation, general parenting skills, skills specific to parenting a child with CHD, and medical issues. Approximately 4 weeks after the workshop, parents receive an individual follow-up session. The baseline (T1) and follow-up assessment (T2 = 6 months after T1) consist of online questionnaires filled out by the child, parents, and teacher (T2 only). Primary outcome measures are the CBCL for children and the SCL-90-R for parents.

**Discussion:**

This trial aims to test the effects of an early family-centered psychosocial intervention to meet the compelling need of young children with CHD and their families to prevent (further) problems. If CHIP-Family proves to be effective, it should be structurally implemented in standard care.

**Trial registration:**

Dutch Trial Registry; NTR6063 on 23 August, 2016.

## Background

Children with congenital heart disease (CHD) are at elevated risk for behavioral, emotional, and cognitive problems in childhood [1, 2], adolescence, and adulthood [3]. Previous cohort studies from our research group have indicated that CHD-children are two times more likely to develop psychopathology than healthy children (16–27% versus 10% in the general population) - irrespective of the type of cardiac defect [4, 5]. Especially internalizing behavior problems, problems with social contacts, and reduced quality of life have been reported [6]. Moreover, neuropsychological problems and intellectual impairments are well known in these children [7, 8] and elevated percentages of CHD-children attending special education (24% versus 4% in norm) have been reported [3]. The most common morbidity affecting the quality of life in school-aged children with CHD is the combination of behavioral/emotional problems, developmental delay, and school difficulties [9]. Such problems can have long-term consequences: two long-term studies have shown that adults with CHD overall had a lower occupational and educational status compared with the general population [10, 11]. Furthermore, children with CHD often have reduced exercise capacity and participate less in exercise and sports, which has been associated with a lower quality of life [12]. It has been shown that participation in an exercise program improves quality of life of children with CHD [13].

In addition, parental factors play a crucial role in children’s psychosocial wellbeing [2, 14–16]. Maternal mental health and worry have appeared to be more important predictors of psychosocial wellbeing of children with CHD than illness severity [2, 17, 18]. Unfortunately, parents of children with CHD are also at risk for psychosocial problems themselves (e.g. anxiety, depression; 1 year prevalence 7–22%) [19].

Considering the above and the fact that milestones such as starting kindergarten and primary school present more challenges for children with CHD and their parents than for families with healthy children [20], a family-based psychosocial intervention tailored to their needs when starting school is required [19, 21, 22]. This need has also been expressed by parents and patients [21, 23]. Through such an intervention, psychosocial problems of children with CHD and their parents may be recognized, reduced or prevented. In addition, school functioning, emotional resilience, and sports participation of these children can be improved [21, 24]. Until now, the only evidence-based intervention in this field is the Congenital Heart Disease Intervention Program (CHIP) – School [2]. The CHIP-School study aimed to promote psychosocial wellbeing of preschoolers with CHD indirectly by providing an intervention for their parents. CHIP-School resulted in significant gains in maternal mental health, reduced perceived strain on the family, and less school absence of the child. As to child psychosocial wellbeing, only a non-significant, though positive, trend was found [2].

A limitation of CHIP-School was that a separate child module was not included. Therefore, in collaboration with the original authors of the previous CHIP intervention, we have translated, extended and modified CHIP, by adding a tailored child module for CHD-children and their siblings. The child module includes evidence-based cognitive behavioral exercises [25] and sports exercises. The newly developed CHIP-Family is a psychosocial intervention for 4- to 7-year-old children who have undergone at least one medical intervention for CHD and are starting or attending kindergarten or primary school (first or second year) and their families.

The aim of this study is (1) to test the effects of CHIP-Family on parental mental health and psychosocial wellbeing of CHD-children who are starting or attending kindergarten or primary school and to (2) identify baseline psychosocial and medical predictors for the effectiveness of CHIP-Family.

## Methods

This study is a single-center, single-blinded randomized controlled trial (RCT) comparing the effects of the CHIP-Family intervention with care as usual (CAU; regular medical treatment) on mental health of parents and psychosocial wellbeing of young children with CHD. This RCT is designed according to the CONSORT guidelines [26].

### Inclusion and exclusion criteria

Over a one-year period (September 2016 – September 2017) children and their families living in the Netherlands will be recruited. Eligible are all children who (1) underwent at least one invasive procedure (catheter intervention or surgery) for CHD and (2) are starting or attending kindergarten or primary school (first or second year) at the time of first assessment (as the children are approximately 4–7 years old). Exclusion criteria are: (1) child’s intellectual impairment (IQ < 70) as ascertained by previous standardized assessment or diagnosed by a clinician, (2) insufficient mastery of the Dutch language, and (3) prematurely born children (gestational age at birth < 37 weeks) with no other CHD than a patent ductus arteriosus.

### Recruitment and procedure

Parents of 4- to 7-year-old children who receive treatment at the department of pediatric cardiology of the Erasmus Medical Center – Sophia Children’s Hospital and eligible members of the Dutch Patient Association for Congenital Heart Disease whose children receive treatment in a cardiac centre in the Netherlands will receive an information leaflet explaining the purpose and procedures of the study. Before inclusion, parents will receive a verbal explanation of the trial. After obtaining written parental informed consent, patients are randomly allocated to the CHIP-Family intervention or CAU group. To avoid a delay of more than 1 month between baseline assessment and the intervention, patients are randomized prior to the baseline assessment. Patients are allocated to the CHIP-Family intervention or CAU group by means of block randomization, performed by an independent researcher. Randomization will be stratified by CHD severity (limited to no residual heart defects or moderate to severe residual heart defects [after medical intervention]; see Table 1) and school year (kindergarten or primary school). To avoid bias, the researcher performing the assessments and analyses will be blinded. Considering the nature of the CHIP-Family intervention, it is not possible to blind the participants and the health care professionals providing the intervention.

**Table 1 Tab1:** Stratification factor “CHD severity”

Type 1	Type 2
Limited to no residual heart defects after medical intervention	Moderate to severe residual heart defects after medical intervention
Atrial Septal Defect (ASD)	ALCAPA (Anomalous Left Coronary Artery from the Pulmonary Artery)
Patent Ductus Arteriosus	Aortic Valve Stenosis
Pulmonary valve stenosis	Atrioventricular Septal Defect (AVSD)
Total Anomalous Pulmonary Venous Connection	Coarctation of the Aorta
Ventricular Septal Defect (VSD)	Complex Biventricular (e.g. Truncus Arteriosus, aortic arch defects)
	Double Inlet Ventricle – Fontan circulation
	Ebstein’s Anomaly
	Subvalvular Aortic Stenosis
	Tetralogy of Fallot (TOF)
	TOF with MAPCA (Main Aorta to Pulmonary Connecting Artery)
	Transposition of the Great Arteries

### Intervention

CHIP-Family consists of a parent module and a child module. Parents and children participate in a separate, but simultaneously given, 6-h group workshop. An overview of the content of the workshops is given in Table 2. Over the course of a 11-month period (Nov. 2016 – Sept. 2017) 11 workshops will be given to 3 to 5 families per workshop.

**Table 2 Tab2:** Outline of the CHIP-Family workshops

Health care professional(s)	Content
Parent workshop	
Psychologists	• Problem prevention therapy [48]. A DO ACT acronym is applied: **D**efine problem and turn into a specific goal; **O**ption brainstorm; **A**ssess pros and cons of various options; **C**hoose a strategy; **T**ake action and evaluate
	• Psychoeducation
	• General parenting skills
	• Specific parenting skills for children with CHD
Pediatric cardiologist	• Information on medical diagnoses, treatments, future issues (e.g., career, pregnancy), insurance, and healthy living (e.g., sports, diet)
Child workshop	
Psychologists	• Relaxation
	• Promoting autonomy
	• Strengthening self-esteem
	• Making friends
	• Problem solving skills
	• Positive thinking
Physiotherapists	• Playful, age-attuned sports exercises: warming-up, fitness, gross motor skills, balance, aiming, and catching

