#### Workshop

The parent workshop focuses on problem prevention therapy, psychoeducation, general parenting skills, skills specific to parenting a child with CHD (given by two senior psychologists with expertise in the field; 4 h), and medical issues (given by a pediatric cardiologist; 1 h). The lunch break (1 h) offers families more opportunity to interact and share (similar) experiences. During the workshop, parents receive a manual which contains an overview of the topics that will be covered during the workshop and a home assignment on problem prevention therapy. Parents also receive handouts and a teacher information leaflet.

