### Sample size calculation

To conduct a repeated measures ANOVA with two assessment moments, Cohen’s d of 0.6, an alpha of .05 (two-tailed), and a power of .80, a sample size of 90 patients is needed, of which 45 patients in the intervention group.

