### Statistical analysis

To test the effectiveness of CHIP-Family on the primary outcome measures (for parents: mental health [SCL-90-R]; for children: behavioral/emotional problems [CBCL]) repeated measures ANOVAs will be conducted, for parental and child outcomes separately. Group (CHIP-Family versus CAU) will be the between-subjects variable and assessment (T1 versus T2) will be the within-subjects variable. Likewise, repeated measures ANOVAs will be conducted for the secondary outcome measures.

Additional regression analyses will be conducted to investigate in what way demographic factors, medical factors, and life events moderate the effect of CHIP-Family on the primary outcome measures.

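### The primary ANOVA and the sample size treat families as independent, although CHIP-Family is delivered in 11 shared workshops in one arm only

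*Protocol article*

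**What the plan says.** In the protocol article, the Recruitment and procedure section randomizes patients individually. The Intervention section then describes group delivery: "Parents and children participate in a separate, but simultaneously given, 6-h group workshop", and "11 workshops will be given to 3 to 5 families per workshop". The parent Workshop section adds that the lunch break "offers families more opportunity to interact and share (similar) experiences". Care as usual has no group treatment.

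The Statistical analysis section fixes the primary model: "Group (CHIP-Family versus CAU) will be the between-subjects variable and assessment (T1 versus T2) will be the within-subjects variable". It names no workshop or family term.

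The Sample size calculation section starts from "To conduct a repeated measures ANOVA with two assessment moments", with "Cohen’s d of 0.6", two-sided alpha 0.05 and power 0.80, and concludes that "a sample size of 90 patients is needed, of which 45 patients in the intervention group". It mentions no allowance for clustering.

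Table 3 shows that both parents complete both primary outcomes (CBCL and SCL-90-R) at T1 and T2. The article separates parental from child outcomes but does not say how the two parents' reports are combined.

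**The concern.** Families who share a workshop share its group composition, its discussion and one of its psychologists. Their outcomes after the workshop may therefore resemble each other more than those of families in different workshops. Individual randomization does not remove this, because the grouping arises after allocation and in one arm only.

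An error term built from between-family variation then understates the variance of the CHIP-Family mean. Confidence intervals for the primary comparison are too narrow, the test rejects too often, and a valid test has less power than stated. A separate, conditional question is whether two parents of the same child could enter the analysis as if they were unrelated subjects.

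**Working it through.** **Inputs from the article.** d = 0.6; two-sided alpha 0.05; power 0.80; 45 per arm; 11 workshops of 3 to 5 families in the CHIP arm. Capacity is 11 × 3 = 33 to 11 × 5 = 55 families, and the mean size is m = 45/11 = 4.09.

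**Assumed.** Workshop ICC from 0.01 to 0.20, on whichever scale d refers to. The article does not say whether d is on the T2 score or on change.

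**Step 1: reproduce the plan's figure.** A two-sample t-test with d = 0.6 needs 44.6, so 45 per arm and 90 in all. Power at 45 per arm is 0.804 (t) or 0.812 (normal approximation). The stated N is that of independent patients, with no reserve.

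**Step 2: cluster the CHIP arm only.**
- Design effect in the CHIP arm: DE = 1 + (m − 1) × ICC
- True SE, in SD units: √(DE/45 + 1/45)
- Plan's SE: √(2/45) = 0.211
- SE ratio: √((DE + 1)/2)
- Type I error of the plain test: 2 × [1 − Φ(1.96 / SE ratio)]
- Valid power (z): Φ(0.6/SE − 1.96)
- Valid power (t): noncentral t with Satterthwaite degrees of freedom based on 11 workshops (about 24 to 32 here)

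Example at ICC 0.10: DE = 1 + 3.09 × 0.10 = 1.309. The SE ratio is √(2.309/2) = 1.074, so SE = 0.2265. Type I error is 2 × [1 − Φ(1.824)] = 0.068. Power (z) is Φ(2.649 − 1.96) = 0.755.

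| ICC (assumed) | DE | SE ratio | Type I error, plain test | Valid power, z | Valid power, t |
|---|---|---|---|---|---|
| 0 (plan) | 1 | 1 | 0.050 | 0.812 | 0.804 (plain t-test) |
| 0.01 | 1.031 | 1.008 | 0.052 | 0.806 | 0.782 |
| 0.02 | 1.062 | 1.015 | 0.054 | 0.800 | 0.775 |
| 0.05 | 1.155 | 1.038 | 0.059 | 0.783 | 0.756 |
| 0.10 | 1.309 | 1.074 | 0.068 | 0.755 | 0.724 |
| 0.20 | 1.618 | 1.144 | 0.087 | 0.701 | 0.665 |

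**Step 3: check by simulation.** This used 20,000 trials per ICC, with ten workshops of four families and one of five against 45 unclustered families. At ICC 0.05, 0.10 and 0.20 the plain test's type I error was 5.9%, 7.0% and 9.1%. Power of a workshop-mean test was 0.746, 0.720 and 0.662. This agrees with the table.

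**Step 4: sample size (z approximation).** n per arm = (DE + 1) × ((1.96 + 0.84)/0.6)². With m from 4.09 to 5 this gives 47 to 48 at ICC 0.05 and 51 to 53 at ICC 0.10.

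**Step 5: parents, only if pooled as independent subjects.** With within-couple correlation ρ (assumed), DE = 1 + ρ and type I error = 2 × [1 − Φ(1.96/√(1 + ρ))]. This is 8.6% at ρ = 0.3 and 11.0% at ρ = 0.5. Leaving workshop clustering aside, power with 45 two-parent families per arm has an effective n of 90/(1 + ρ) per arm. That is 69 at ρ = 0.3 (power 0.94) and 60 at ρ = 0.5 (power 0.91), both above 0.80.

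**The case against.** **The ICC may be small.** The Training and protocol adherence section keeps one senior and one junior psychologist constant across workshops, standardizes delivery and checks integrity. Contact is one day plus an individual booster session, and T2 comes six months after T1. At ICC 0.01 to 0.02 the harm is negligible, and about 2 points of the power drop in the t column come only from the degrees of freedom of the workshop-mean test. This stands as an argument about size. It does not show that the ICC is zero: each workshop also has a further psychologist, and group composition differs.

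**Enrolment waves are shared.** The Outcome measures section enrols both arms together in groups of 6 to 10 families, so calendar effects largely cancel from the contrast. A simulation that put a correlation of 0.10 wholly into the shared wave gave the plain test a type I error of 4.0%, which is conservative. This stands: only workshop-specific variation inflates the error. If the intervention affected nobody, delivery would create no clustering, so the inflation concerns workshop effects that vary but average to zero.

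**A stronger reading is tempting.** A reader might infer that the ANOVA treats every observation as independent. It does not, because T1 and T2 on the same subject are linked by the within-subjects factor. A reader might also infer that mothers and fathers are entered as separate subjects and that this overstates power. The article states no such pooling. Separate or averaged analyses would not cause this inflation, and how the reports are combined may be set out in an analysis plan that is not shown. The N counts patients, one per family, and a second correlated parent cannot lower power below that of 45 families per arm.

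**Conclusion.** The point holds for workshops. The article fixes both a primary model and an N that ignore the grouped delivery it describes. With any positive workshop-specific ICC the standard error is too small, by about 4% at ICC 0.05 and 7% at 0.10, and the 80% power is overstated by roughly 2 to 8 points over that range. The figures rest on an assumed ICC, about four families per workshop, and no clustering in the care-as-usual arm.

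The parent part is conditional. It concerns type I error, not power, and applies only if both parents' reports are pooled as independent. Severity is moderate: clusters are small, only one arm is affected, and the loss nearly vanishes at the low end of the ICC range.

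**What to change.** - Record the workshop number for every CHIP-Family participant.
- Analyse each primary outcome with a partially nested mixed model that has a random workshop effect in the CHIP arm only, with Satterthwaite or Kenward-Roger degrees of freedom.
- Let that effect act on T2 or on change, through a workshop-by-time term or a T2 model adjusted for T1. T1 precedes the workshop, so a workshop intercept that is constant over time largely cancels from the group-by-time contrast and would leave its standard error essentially uncorrected.
- If mothers' and fathers' reports are analysed together, add a family random effect with parent as a fixed factor. Otherwise state that they are analysed separately or averaged.
- Restate power over an ICC range such as 0.01 to 0.10. The 47 to 53 CHIP families that the z approximation gives for ICC 0.05 to 0.10 fit within the planned workshop capacity of 55, if the sponsor wishes to restore 80%.

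The cost is a change of analysis wording and one extra recorded variable, with slightly wider intervals and a slightly lower stated power.

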### Parent module

The parent module is based on the evidence-based CHIP-School protocol [2].

#### Workshop

The parent workshop focuses on problem prevention therapy, psychoeducation, general parenting skills, skills specific to parenting a child with CHD (given by two senior psychologists with expertise in the field; 4 h), and medical issues (given by a pediatric cardiologist; 1 h). The lunch break (1 h) offers families more opportunity to interact and share (similar) experiences. During the workshop, parents receive a manual which contains an overview of the topics that will be covered during the workshop and a home assignment on problem prevention therapy. Parents also receive handouts and a teacher information leaflet.

#### Follow-up booster session

Approximately 4 weeks after the workshop, parents receive an individual follow-up booster session with a psychologist who was present during the parent workshop and a psychologist who was present during the child workshop. Questions or worries that may have come up after the workshop regarding their child with CHD or their family members are discussed. Also, aspects of the workshop which have been (most) helpful for parents and will be helpful in the future are reviewed. Moreover, the session focuses on the problem prevention home assignment and on how to promote future use of problem prevention therapy.

### Child module

To normalize participation in the workshop and to stimulate practice at home, each child is allowed to bring a 4- to 10-year-old sibling or friend. The psychological exercises (given by two junior psychologists; 4 h) are based on the evidence-based cognitive behavioral therapy Fun FRIENDS protocol [25]. The exercises are provided in a playful manner and focus on regulating emotions, relaxation, promoting autonomy, strengthening self-esteem, making friends, problem solving skills, and positive thinking. The playful, age-attuned sports exercises (given by a physiotherapist and assistant physiotherapist; 1 h) are based on a standardized training program. Previous research has shown that these exercises are effective in improving the quality of life in children with CHD [13].

### Training and protocol adherence

CHIP-Family is performed in a standardized manner. Prior to the workshops, four senior and five junior psychologists receive a one-day CHIP-training by developmental psychologists Prof. [name] and [name], developers of the original CHIP-protocol. To ensure consistency, the same senior and junior psychologist will be present at each workshop. In both the parent and child workshops, another psychologist will be present. Master’s students in Psychology will assess treatment integrity during the parent and child workshop through a standardized form. Follow-up sessions are audiotaped and treatment integrity is assessed through a standardized form afterwards.

